***9.7. Reporting any deviations from the initial statistical plan***

If the initial study plan requires modifications, all changes will be described and explained in a protocol amendment or interim/final clinical study report.

If initially defined statistical methods cannot be used, the changes should be explained in the final statistical report and the clinical study report. Justification of these changes should be given with the references to calculations, statistical parameters, and analysis of a situation that led to these changes. Decisions regarding emergency deviations (data-modifying allowances) can be made only by the Sponsor. These decisions must be explained and justified, including in the final study report.

### ***9.8. Selection of subjects for analysis***

#### ***Efficacy analysis***

To assess whether the study has achieved its objective and to evaluate the treatment efficacy, the analysis will be performed in two populations: the ITT (intent-to-treat) population (all randomized patients) and the PP (per protocol) population (includes subjects who have no major protocol deviations up to and including Week 16).

#### ***Safety analysis***

The safety population will include all randomized patients (ITT population). In addition, the study report will contain data on serious adverse events reported during screening (if any).

#### ***Immunogenicity analysis***

The immunogenicity analysis will include all patients who received at least one dose of BCD-057/Humira®. Patients whose serum samples taken on Day 1 of Week 0 and at least one serum sample taken on any subsequent visit (weeks 16, 33, and 55) are missing/lost/spoiled, will be removed from the immunogenicity analysis.

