|                             | 
WBC differential, and ESR; blood biochemistry: glucose, bilirubin total, ALT, AST, GGT, alkaline phosphatase, and creatinine; urinalysis), cardiac disorders (ECG), and pulmonary conditions (chest X-ray and/or fluorography)).
 
 
Immunogenicity of adalimumab (occurrence of binding/neutralizing anti-adalimumab antibodies) will be assessed in both treatment arms regularly throughout the study (before dosing and at weeks 16, 33, and 55). The assay will be performed at the BIOCAD Central Laboratory.
 
 
Additional blood specimens for PK assessment will be collected from a limited population (not more than 90 patients in each arm; not more than 180 patients total).
                                                                                                                                                                                                                                                                                                                                                                                                                                                                                  |
| Total Study Duration | 
The expected duration of the study is 30 months. This includes patient recruitment (up to 12 months), treatment period, follow-up period, and collection and statistical processing of results.
 
Each subject will participate in the study for up to 59 weeks (about 14 months), including 4 weeks of screening, 51 weeks of treatment, and 4 weeks of follow-up.
                                                                                                                                                                                                                                                                                                                                                                                                                                                                                                                                                                                                                                                                                                                                                                                                                                                      |

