| Statistical Analysis | 
Methods of analysis
 
Statistical analysis will be performed with the Statistica 10.0 software. The normally distributed data will be analyzed using the dependent-sample t-test and ANOVA. The non-normally distributed data will be analyzed using the Mann-Whitney test and ANOVA. The regression analysis will be applied for quantitative efficacy data. Non-categorical data will be processed using the Fisher's exact test, Yates-corrected <math>\chi^2</math> test and Cochran-Mantel-Haenszel test.
 
Determination of sample size
 
The purpose of the study is to demonstrate that the efficacy of BIOCAD's adalimumab biosimilar (BCD-057) is equivalent to the efficacy of Humira® in patients with psoriasis. The number of subjects was determined with the formula for calculating the sample size in two parallel-group equivalence studies as described in the [Chow Shein-Chung, Shao Jun, Wang Hansheng "Sample Size Calculations in Clinical Research"].
 
Selection of populations for analysis
 
Efficacy analysis
 
To assess whether the study has achieved its objective and to evaluate the treatment efficacy, the analysis will be performed in two populations: the ITT (intent-to-treat) population (all randomized patients) and the PP (per protocol) population (includes subjects who have no major protocol deviations up to and including Week 16). If the patient is withdrawn from the study due to safety-related reasons before the primary endpoint is assessed, he/she will be included in the efficacy analysis and considered a non-responder.
 
Safety analysis
 
The safety population will include all randomized patients (ITT population). In addition, the study report will contain data on serious adverse events reported during screening (if any).
 
Immunogenicity analysis
 
The immunogenicity analysis will include all patients who received at least one dose of BCD-057/Humira®. Patients whose serum samples taken on Day 1 of Week 0 and at least one serum sample taken on any subsequent visit (weeks 16, 33, and 55) are missing/lost/spoiled, will be removed from immunogenicity analysis.
 
PK analysis
 
The PK study will involve a limited population (90 patients from each study arm, 180 subjects total). The PK analysis will include all of these 180 patients who:
 
 
Completed all visits for PK assessment starting from Day 1 of Week 15 to Day 6 of Week 16, except for those who missed more than two PK blood samplings during this period.
 
 |

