#### **8.5. Immunogenicity study**

Immunogenicity of BCD-057/Humira® will be assessed using the proportions of patients who develop antibodies to adalimumab (binding and/or neutralizing).

The immunogenicity analysis will include all patients who received at least one dose of BCD-057/Humira®. Patients whose serum samples taken on Day 1 of Week 0 and at least one serum sample taken on any subsequent visit (weeks 16, 33, and 55) are missing/lost/spoiled, will be removed from immunogenicity analysis.

Immunogenicity of BCD-057/Humira will be assessed by evaluating titers of binding and neutralizing anti-adalimumab antibodies (BAbs and NABs).

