#### ***Immunogenicity:***

- The proportion of patients with binding or neutralizing anti-adalimumab antibodies.
- The proportion of patients with binding or neutralizing anti-adalimumab antibodies and inadequate therapeutic response (achieved PASI 50 or less).

The categorical data will be processed using frequency tables, contingency tables, exact Fisher's test, test for equality of frequencies,  $\chi^2$  test, and Cochran-Mantel-Haenszel test. The categorical data will be described using percentages or proportions.

Correction for multiple comparisons will be performed with the Benjamini-Yekutieli procedure.

Statistical methods will be chosen based on the type and distribution of raw data. Appropriate statistical methods will be determined when all the data are obtained, since data distribution and sample homogeneity cannot be assessed in advance. A list of methods may be expanded if necessary for conducting a high-quality study.

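### As worded, the immunogenicity removal rule keeps dosed patients with no post-baseline antibody sample and admits readings that give different populations

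*Protocol*

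**What the plan says.** Section 9.8 (Immunogenicity analysis) starts from everyone treated: "The immunogenicity analysis will include all patients who received at least one dose". It then removes some of them. The removal sentence opens "Patients whose serum samples taken on Day 1 of Week 0 and at least one serum sample taken on any subsequent visit" and closes "weeks 16, 33, and 55) are missing/lost/spoiled, will be removed from the immunogenicity analysis". Section 8.5 repeats the rule, starting from "The immunogenicity analysis will include all patients who received at least one dose of BCD-057/Humira" and ending "are missing/lost/spoiled, will be removed from immunogenicity analysis". The Synopsis (Statistical Analysis) repeats it again, ending "will be removed from immunogenicity analysis". The construction is the same in all three places, so it is not a slip in one of them.

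Other parts of the protocol that bear on the rule:

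- Antibody samples are taken "before dosing and at weeks 16, 33, and 55" (Synopsis, Study Procedures; Table 19 agrees).
- The first immunogenicity endpoint is "The proportion of patients with binding or neutralizing anti-adalimumab antibodies" (section 9.1). The second is the proportion with antibodies and an inadequate response.
- The Early Termination Visit in section 5.4.1 covers concomitant therapy, physical examination, blood pressure and temperature. It lists no antibody sample.
- Section 5.4.2 keeps in the analysis the data of anyone withdrawn after at least one dose.
- Section 9.6 says that missing data are not replaced.

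**The concern.** A set for estimating antibody incidence should contain patients in whom an antibody could have been detected after dosing. The word that joins the two conditions in the removal sentence works against this. It makes removal depend on losing the baseline sample and a later one together. A patient with a sound baseline sample is never removed, even with no later sample at all.

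The protocol's own procedures can produce such patients. The first post-dose sample is at Week 16, withdrawal before then is possible, and the withdrawal visit lists no antibody sample.

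Both immunogenicity endpoints are proportions of patients, and immunogenicity is a stated objective of this biosimilar comparison. The rule decides who can be in the denominator. Because the sentence supports more than one population, the choice among them could also be made after the results are known.

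**Working it through.** The plan states no figure on this point, so there is none to reproduce. The check has two parts.

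**1. Who is kept under each reading.** Each of the four samples (Weeks 0, 16, 33, 55) is present or missing, which gives 2⁴ = 16 patterns. Three readings of the sentence:

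- A, as written: remove if Week 0 is missing and at least one later sample is missing.
- B, possible intent: keep only if Week 0 is present and at least one later sample is present.
- C, strict: remove if any sample is missing.

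| Pattern (Week 0; later samples) | Number of patterns | A | B | C |
|---|---|---|---|---|
| Present; all three present | 1 | keep | keep | keep |
| Present; one or two present | 6 | keep | keep | remove |
| Present; none present | 1 | **keep** | remove | remove |
| Missing; all three present | 1 | **keep** | remove | remove |
| Missing; one or two present | 6 | remove | remove | remove |
| Missing; none present | 1 | remove | remove | remove |

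Patterns kept: A 1 + 6 + 1 + 1 = 9, B 1 + 6 = 7, C 1. A and B agree on 14 of 16 and differ in the two rows in bold. These are counts of patterns, not of patients, and the patterns are not equally likely.

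Under A, a patient without a baseline sample is kept when all three later samples exist, but removed when one of them is lost, even if another is positive.

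**2. Size of the effect if unsampled patients are counted.** Let r be the antibody rate among patients with a post-baseline sample. Let m be the share of the denominator with no such sample. These patients add to the denominator and nothing to the numerator, so

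reported rate = r × (1 − m), and the loss is r × m.

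Inputs: r = 8.4% is the originator rate quoted in section 1.4.2, and r = 20% is an assumed higher value. The protocol does not give m, so 2% to 15% is an assumed range.

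| m | r = 8.4% | r = 20% |
|---|---|---|
| 2% | 0.084 × 0.98 = 8.2% | 0.20 × 0.98 = 19.6% |
| 5% | 0.084 × 0.95 = 8.0% | 0.20 × 0.95 = 19.0% |
| 10% | 0.084 × 0.90 = 7.6% | 0.20 × 0.90 = 18.0% |
| 15% | 0.084 × 0.85 = 7.1% | 0.20 × 0.85 = 17.0% |

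If the arms have equal true rates but m is 5% in one and 10% in the other, the artificial difference is r × (0.10 − 0.05). That is 0.4 points at 8.4% and 1.0 point at 20%.

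**The case against.** The strongest reply is that the sentence is only clumsy. A baseline sample plus at least one later sample is a usual way to describe an evaluable set, and the authors may have turned that phrase into the negative without changing the conjunction. On that reading, patients with no post-baseline sample are removed and the main problem disappears. This may well be the intent, but the text does not say so, and the three places repeat the same wording. Section 5.4.2, which keeps the data of every withdrawn patient who was dosed, fits the wording as it stands.

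A reader might infer that the plan scores unsampled patients as antibody-negative, so that the rates will be diluted. The documents do not support this. No passage assigns a negative result, and the no-replacement rule in section 9.6 points away from it. Equally, declining to impute does not take a patient out of a defined population. Whether such patients count in the denominator is left open, so dilution is conditional.

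A reader might also infer that every reading biases the rates downward. That is not shown. Reading C is a complete-case analysis, and the direction of its bias depends on who leaves. Section 1.4.2 says that antibody-positive patients responded less well, so leavers need not be a random subset. However, lack of efficacy is not itself a listed withdrawal criterion.

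Two more points stand. The pattern with no baseline but all later samples should be rare, because section 6.3 does not allow the first blood sampling to be missed; it would mainly arise from a lost or spoiled tube. The effect is also small beside sampling error: with 172 per arm, the 95% half-width around 8.4% is 1.96 × √(0.084 × 0.916 / 172) ≈ 4.1 points. No margin for immunogenicity appears in the visible text.

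**Conclusion.** The point holds as a defect in a stated population rule, not as a detail left to the SAP. Read as written, the rule keeps two kinds of patient who do not belong in an estimate of treatment-emergent antibodies: those with no post-baseline sample, and those with no baseline but all later samples. The same sentence can be read in at least two other ways that give different sets.

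The consequence for the rates is conditional and modest. If patients without a post-baseline sample are counted in the denominator, the loss is r × m. For m from 2% to 15%, that is 0.2 to 1.3 points at 8.4% and 0.4 to 3.0 points at 20%. The range for m and the 20% rate are assumptions. A difference between arms arises only if early loss differs between them, which cannot be known in advance. The rule should be corrected, but the primary endpoint is not affected.

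**What to change.** Replace the removal sentence in the Synopsis, section 8.5 and section 9.8 with one definition: the immunogenicity set is all dosed patients with at least one evaluable post-baseline antibody sample, whatever other samples are missing. Add that treatment-emergent antibodies are reported among those who also have an evaluable Week 0 sample, and that each proportion uses the number tested as its denominator.

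Under this definition a patient with no baseline but a usable later sample counts towards overall antibody presence and not towards the treatment-emergent rate. A patient with only a baseline sample counts in neither. The cost is one rewritten rule in three places, with no new visits, samples or data. It should be made before unblinding.

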#### ***PK analysis***

The PK study will involve a limited population (90 patients from each study arm, 180 subjects total). The PK analysis will include all of these 180 patients who:

- Completed all visits for PK assessment starting from Day 1 of Week 15 to Day 6 of Week 16, except for those who missed more than two PK blood samplings during this period.
- Provided a blood specimen for adalimumab assay on Day 1 of Week 0 (before the first injection of BCD-057/Humira®);
- Missed not more than one dose of adalimumab within the period from the study start to Week 15 inclusive (injections 1 to 9).

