## Abbreviations

|                       |                                                                                                                                                                   |
|-----------------------|-------------------------------------------------------------------------------------------------------------------------------------------------------------------|
| AE                    | Adverse event                                                                                                                                                     |
| AlkPh                 | Alkaline phosphatase                                                                                                                                              |
| ALT                   | Alanine aminotransferase                                                                                                                                          |
| APTT                  | Activated partial thromboplastin time                                                                                                                             |
| AST                   | Aspartate aminotransferase                                                                                                                                        |
| AUC                   | Area under the concentration vs. time curve                                                                                                                       |
| AUC tau,ss | Area under the concentration-time curve during a dosing interval at steady state                                                                                  |
| BAbs                  | Binding antibodies                                                                                                                                                |
| BB                    | Blood biochemistry                                                                                                                                                |
| BCG                   | Bacillus Calmette-Guérin                                                                                                                                          |
| BMI                   | Body mass index                                                                                                                                                   |

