This study is to compare the pharmacokinetics of BCD-057 and Humira® in a limited patient population (90 subjects from each study arm, 180 subjects total). This investigation is necessary to demonstrate that pharmacokinetics of these drugs is similar not only in healthy volunteers but in psoriasis patients as well (who may differ from healthy subjects in terms of adalimumab PK). In patients with plaque psoriasis, adalimumab is used for a long time, so it is important to study its PK parameters at steady state – when an equilibrium between the intake of the drug and its elimination has been achieved. Adalimumab fully exerts its clinical effects when reaches the steady state concentration. In addition, steady-state PK allows predicting how rapidly the serum levels of the active ingredient decrease is the patient misses a dose or discontinues the drug.

It is known that the time to steady state equals 3 to 5 half-life periods of adalimumab. For adalimumab, the average half-life is 2 weeks, varying from 10 to 20 days [8]. Thus, the maximum time to steady state will be 100 days or 14.3 weeks ( $20 \times 5 = 100$ ). According to literature data, adalimumab concentrations reach the steady state in 12 to 16 weeks. Blood specimens will be

---

 Adalimumab M04-688 Pharmacokinetic Report

[http://www.abbvie.com/assets/research/clinical-trials-data-and-information-sharing/synopses/adalimumab\\_M04-688.pdf](http://www.abbvie.com/assets/research/clinical-trials-data-and-information-sharing/synopses/adalimumab_M04-688.pdf)

taken at frequent intervals after the 9th injection of adalimumab (at weeks 15 and 16), and thus the PK of BCD-057/Humira® will be studied at steady state.

In the second period of the study, some patients will be crossed over from one drug product to another. After completing Week 24 and all appropriate assessments, one half of patients from the Humira® arm will be switched to BCD-057. The rest of patients who were originally randomized to receive Humira® will continue the treatment with Humira®.

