|                           |                                                                                      | Day 2 of Week 15, 24 h $\pm$ 30 min after the 9 th injection of adalimumab (PK11),
Day 3 of Week 15, 48 h $\pm$ 90 min after the 9 th injection of adalimumab (PK12),
Day 4 of Week 15, 72 h $\pm$ 120 min after the 9 th injection of adalimumab (PK13),
Day 5 of Week 15, 96 h $\pm$ 120 min after the 9 th injection of adalimumab (PK14),
Day 6 of Week 15, 120 h $\pm$ 120 min after the 9 th injection of adalimumab (PK15),
Day 7 of Week 15, 144 h $\pm$ 120 min after the 9 th injection of adalimumab (PK16),
Day 2 of Week 16, 192 h $\pm$ 120 min after the 9 th injection of adalimumab (PK17),
Day 4 of Week 16, 240 h $\pm$ 120 min after the 9 th injection of adalimumab (PK18),
Day 6 of Week 16, 288 h $\pm$ 120 min after the 9 th injection of adalimumab (PK19),
Day 1 of Week 17, 15 min before the injection of adalimumab (PK20),
Day 1 of Week 19, 15 min before the injection of adalimumab (PK21),
Day 1 of Week 21, 15 min before the injection of adalimumab (PK22),
Day 1 of Week 23, 15 min before the injection of adalimumab (PK23), |                                                        |

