##### ***Patients involved in the PK study***

Any deviations from the visit schedule are strongly discouraged. If necessary, the visit can be postponed for 3 days within the following periods: From Visit 1 (Week 0) to Visit 8 (Week 13) and from Visit 11 (Week 17) to Visit 14 (Week 23).

**Deviations from the visit schedule starting from Visit 9 (Week 15) and to Visit 10-3 (Day 6 of Week 16) are allowed only due to AEs/SAEs.**

Starting from Visit 15 (Week 24), visits can be postponed for not more than 7 days due to any reasons not related to therapy. This period can be extended if the investigator provides an appropriate justification and the Sponsor approved re-scheduling.

If the second or subsequent doses of BCD-057 are postponed, the dates of the next visits will be postponed to account for the actual date of the postponed dose, according to the study schedule. If the Protocol stipulates no injection on the postponed visit, the subsequent visits are performed according to the original schedule.

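### The PK analysis set treats a missed injection 8 like a missed injection 1 and does not require the 336 h sample that closes the profiled interval

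*Protocol*

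**What the plan says.** Section 9.8 (PK analysis), and the same text in the synopsis, sets three criteria for the PK set.

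- Attendance and sampling: "Completed all visits for PK assessment starting from Day 1 of Week 15 to Day 6 of Week 16". An exception then removes anyone lacking three or more of the samples in that window. Read naturally, up to two may be absent.
- A sample before the first injection.
- Dosing: "Missed not more than one dose of adalimumab within the period from the study start to Week 15 inclusive (injections 1 to 9", with no condition on which dose it is.

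Section 4.1.2 lists AUCtau,ss first among the PK endpoints, and the abbreviations define it as "Area under the concentration-time curve during a dosing interval at steady state". Section 1.5.1 explains why the rich sampling follows the 9th injection: "the average half-life is 2 weeks, varying from 10 to 20 days", steady state takes 3 to 5 half-lives, and this is at most 100 days or 14.3 weeks. Under section 6.1.3.1 missed doses are not made up.

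In Table 19 the last sample inside the window of the first criterion is PK19 ("Day 6 of Week 16, 288 h" after the 9th injection). The next one closes the dosing interval: "Day 1 of Week 17, 15 min before the injection of adalimumab (PK20". No criterion in section 9.8 mentions it.

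**The concern.** The endpoints describe one 14-day interval at steady state, and section 1.5.1 rests that on an unbroken dosing sequence up to injection 9. A rule that only counts misses ignores their position. A miss at Week 0 has washed out by Week 15. A miss at Week 13 leaves 28 days between injections 7 and 9, two average half-lives, immediately before the profile. The interval also needs a value at its end, and the sampling criterion stops 48 h short of it.

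At stake is the steady-state comparison that section 1.5.1 calls necessary to show similar PK in patients and not only in healthy volunteers. Values lowered by a dosing gap add noise unrelated to the products. They can shift the ratio if gaps are more frequent in one arm.

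**Working it through.** **The protocol's own figure.** 5 × 20 days = 100 days, and 100/7 = 14.3 weeks, as stated. Injection 9 falls on day 15 × 7 = 105. At the longest half-life the margin is 5 days, and only if all doses were given.

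**Clock.** Day 6 of Week 16 is (7 + 5) × 24 = 288 h after injection 9. Day 1 of Week 17 is 14 × 24 = 336 h.

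**Inputs.** Regimen: 80 mg at Week 0, then 40 mg at Weeks 1, 3, …, 15 (section 6.1.1), so injection 8 is Week 13 and injection 9 is Week 15. Half-life h = 10, 14 and 20 days (section 1.5.1). The absorption half-life is not in the protocol; I assume instantaneous absorption first, then 1, 2 and 3 days.

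**Formulas.** Linear one-compartment superposition with instantaneous absorption and r = 2^(−14/h), as shares of the steady-state AUCtau:

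- injection 8 missed: loss = r(1 − r)
- injection 1 missed (80 mg, 105 days earlier): loss = 2 × 2^(−105/h) × (1 − r)
- share of AUCtau lying between 288 and 336 h: (2^(−12/h) − 2^(−14/h)) / (1 − 2^(−14/h))

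| h | r | Injection 8 missed | Injection 1 missed | 288–336 h share |
|---|---|---|---|---|
| 10 d | 0.379 | 23.5% | 0.1% | 9.1% |
| 14 d | 0.500 | 25.0% | 0.6% | 10.4% |
| 20 d | 0.616 | 23.7% | 2.0% | 11.5% |

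With no missed dose, the AUC after injection 9 is 100% of the steady-state value at all three half-lives.

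**With the assumed absorption half-lives (0 to 3 days).** Injection 8 missed: AUCtau 24–32% low. Injection 1 missed: still about 2% at most. The 288–336 h share: 9–13%. If the 240 h and 288 h samples are the two permitted absences and the 336 h sample is also missing, the observed part, 0–192 h, is 59–69% of AUCtau.

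**Effect on the comparison.** If a share f of one arm only has AUCtau multiplied by 0.76 (a 24% loss), a ratio of geometric means moves by the factor 0.76^f. For f = 0.05 this is 0.986, a shift of 1.4%; for f = 0.10 it is 0.973, a shift of 2.7%. With 90 patients per arm these shares are 4.5 and 9 patients. The share is an assumption because the protocol gives no rate of missed doses, and the geometric-mean summary is also assumed.

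**Injection 9.** The window of the first criterion holds 12 samplings, PK8 to PK19. Eleven of them, PK9 to PK19, are defined as hours after the 9th injection. A patient without that injection has no sample that meets those definitions, so more than two are missed. Yet the dosing criterion counts injection 9 among the doses that may be missed. The two criteria disagree about the same patient.

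**The case against.** The effect should be small. Study staff give the injections at the site, two consecutive misses lead to withdrawal (sections 4.8.2 and 5.3), and treatment is blinded. Similar miss rates in both arms would mainly add variance. PK is a secondary endpoint. All of this stands, and it is why the size at arm level is modest and conditional. It does not explain why a Week 13 miss should count the same as a Week 0 miss.

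Three stronger readings might be inferred, and the protocol does not support them.

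- A reader might infer that patients who missed the profiled dose enter the PK set, with a loss of 1 − r, that is 38–62% of AUCtau. The wording of the dosing criterion permits this, but the sampling criterion probably excludes such a patient. What remains is an inconsistency to resolve.
- A reader might infer that lacking the 336 h sample takes a patient out of steady state. It only truncates the AUC or forces extrapolation.
- A reader might infer that Ctrough is left outside the criteria. PK8, taken before injection 9, is a trough inside the window, and further pre-dose samples follow up to Week 23. PK8 may, however, be one of the two absences, and after a missed injection 8 it is itself 37–62% low.

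The Week 17 visit may also slip ("the visit can be postponed for 3 days within the following periods"; Weeks 17 to 23 are one of these periods). Whether actual or nominal times are used for a late sample is commonly left to the SAP and is not part of this point.

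**Conclusion.** The point holds for a rule that the protocol itself fixes. The PK set can include a patient who missed injection 8, whose AUCtau is about 24–25% below steady state under instantaneous absorption (24–32% across the assumed absorption range), while the same allowance spent on injection 1 costs at most about 2%. The sampling criterion does not secure the end of the interval, so 9–13% of AUCtau can be unmeasured. The dosing and sampling criteria must be reconciled on injection 9.

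These figures rest on linear one-compartment kinetics and the half-lives in section 1.5.1. It would go too far to say that the steady-state endpoints are computed in patients off steady state, or that the comparison is biased. Such values can enter, and bias needs an imbalance between arms, for which the protocol gives no rate. The sample-size section is largely redacted and no PK acceptance limits are visible, so the effect on the PK conclusion cannot be computed. The correction should be made; it does not touch the primary endpoint.

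**What to change.** Reword the analysis set in section 9.8 and the synopsis only.

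- Require that injection 9 was given and that at least injection 8 was not missed. Allow a single miss only among earlier injections.
- Extend the sampling criterion through PK20 (336 h) for AUCtau,ss.
- Add a sensitivity analysis in patients with no missed dose before the profile.

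How far back the no-miss requirement should reach is partly a matter of preference. If only injections 8 and 9 are required, the worst admitted case is a missed injection 7, with AUCtau 9–17% low over the same half-life and absorption ranges. If injections 7 to 9 are required, the worst case is a missed injection 6, 3–11% low. The sensitivity analysis covers what remains.

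Dosing and visit schedules stay unchanged. The cost is a change of wording and probably a few patients fewer in the PK set; what that does to its power cannot be judged while the sample-size basis is redacted.
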